| Study Type Hypothesis testing |
| Study Design Longitudinal cohort study |
| Feasibility counts There are approximately 5.5 million patients in England, aged 40+ and with up to standard registration for a period between 1/1/1998 to 31/12/2017 in the CPRD GOLD. Restricting to English practices (linked to HES and ONS) and only including patients fulfilling the eligibility criteria listed below, the expected population is approximately 3.3 million and out of these we expect 216,000 fall events, 230,000 myopathy/muscle pain events and 1,200 intracranial haemorrhage events. |
| Sample size considerations We have based our sample size calculation on the least common of the primary outcomes listed above (intracranial haemorrhage), and used the method developed by Riley *et al.,*^40^ to minimise the potential for overfitting and ensure precise estimates of key parameters. A sample size of approximately 80,000 patients is required for the development of a clinical prediction rule for this outcome, assuming an event rate of 24.6 per 100,000 person years,^41^ a median follow up of 7 years,^42^ a conservative estimate of Nagelkerke’s R^2^ statistic of 0.15 and a maximum number of 40 parameters per model.  Feasibility counts showed that this sample size is adequate for the development of the prediction rules. Since Intracranial bleeding is the rarest of the primary outcomes to be studied, the sample size will be sufficient for all other outcomes of interest. For validation, Vergouwe *et al.,*^43^ consider at least 100 events per sample population to be “substantial” and we will comfortably exceed this in our validation cohorts for each outcome of interest.  For analyses using causal inference methods (propensity score matching and instrumental variable analysis), assuming clinically significant increased rate of each adverse event with treatment of 10%, and an event rate of at least 0.5% per year in the non-exposed group, approximately 88,380 patients (44,190 in each group) and 4,634 events will be required to accurately define the relationship between preventative treatment and adverse events, with 90% power and an alpha of 0.05. |

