| Definition of the Study population Individual patient data will be extracted from the medical records of all patients registered at linked general practices contributing to the CPRD GOLD and Aurum in England.  Patients will be included if they meet the following criteria:   - Patients over the age of 40 years - Registered to a CPRD ‘up-to-standard’ practice - Records available after the study start date (01/01/1998) - Sufficient data to define the index date (see table below)   Patients will be excluded if they meet the following criteria:   - Previous prescription of the exposure variable (antihypertensive, statin or antiplatelet) - Blood pressure >180 mm Hg or total cholesterol >7.5 mmol/L (in patients with high blood pressure or cholesterol, treatment is indicated regardless of risk)   Study entry criteria – Patients will enter the cohort on the index date, defined as:   \| **Exposure** \| Antihypertensive therapy \| Statin therapy \| Antiplatelet therapy \| \| --- \| --- \| --- \| --- \| \| **Index date definition** \| 12 months after the first systolic blood pressure reading ≥130 mm Hg \| 12 months after the first coded or calculated CVD risk of ≥5% \| 3 months after first CVD event \|   Study exit criteria   - Last date at which the most recent linked data are available from the CPRD (study end date, July 2018) - Date of the most recent data upload from the practice to which a given patient is registered - Date at which a given patient transfers out of a registered CPRD practice - Date of death or specific outcome of interest |
| Selection of comparison group(s) or controls Aim 1: Not applicable – single cohort in CPRD GOLD.  Aim 2: Not applicable – single cohort in CPRD AURUM.  Aim 3 will use propensity score matching and instrumental variable analysis – see Methods section below. |

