| Exposures, Outcomes and Covariates This study will examine the overall risk of harm from three types of cardiovascular medication: antihypertensives, statins and antiplatelets. ‘Harm’ will be defined by the outcomes listed in the table below, which will be examined both individually and as a composite outcome. The association between treatment and a positive and negative control outcome will also be examined to check the validity of the treatment effect estimates. Positive controls are outcomes know to be affected by treatment (e.g. cardiovascular disease) and negative outcomes are those known not to be affected by treatment.   \| **Variable** \| **Antihypertensive therapy** \| **Statin therapy** \| **Antiplatelet therapy** \| \| --- \| --- \| --- \| --- \| \| Exposure \| ACE inhibitors  Angiotensin II receptor antagonists  Calcium channel blockers  Thiazides and thiazide-like diuretics  Beta blockers  Alpha blockers  Centrally acting antihypertensives  Vasodilators  Renin inhibitors \| Statins \| Aspirin  Clopidogrel  Dipyridamole  Ticagrelor  Prasugrel \| \| Outcome (hospital admission or death due to) \| Falls  Fracture  Syncope  Hypotension (symptomatic)  Acute kidney injury  Electrolyte abnormalities*  Gout  Any adverse event \| Myopathy/muscle pain  Diabetes mellitus  Intracerebral haemorrhage  Cataract  Liver dysfunction  Dementia  Memory problems (including dementia)  Any adverse event \| Intracerebral haemorrhage  Gastrointestinal haemorrhage  Dyspnoea  Any adverse event \| \| Covariates (predictors of outcome and/or treatment) \| Age, sex, BMI, blood pressure, cholesterol, HbA1c, other prescribed medications, co-morbidities, social deprivation, previous adverse events, frailty and proximity to death. \| \| \|   *Defined as any (hyponatraemia, hypokalaemia, hyperkalaemia, hypomagnesaemia, hypophosphataemia hypercalcaemia or hyperuricemia)  All outcomes will be defined according to diagnostic and/or symptom codes, unless otherwise stated. Further sensitivity analyses will explore the impact of our definition of myopathy and muscle pain, focussing on formal diagnostic codes for myopathy only.  Our PPI engagement suggests some patients are concerned about side effects which will result in having to go to hospital, whilst others are more concerned about chronic conditions which affect their daily quality of life. The primary outcomes of this study will therefore be hospital attendance, defined according to ONS and Basic HES datasets. Sensitivity analyses will explore outcomes defined more broadly using primary care codes as well.  All published outputs from this work will be based on the outcomes as specified in this application. Further work with our patient and public involvement representatives will explore definitions of these outcomes and how they should be incorporated into the final calculators developed as part of the wider programme of work related to this project.  Each model will be derived pragmatically, using coded data routinely available in a primary care setting. Potential predictors will be selected based on previous literature and expert opinion.^30 31 44^ Predictors will be defined by codes in the primary care records, using code lists from previous studies (via [www.clinicalcodes.org](http://www.clinicalcodes.org)). Each model will also incorporate basic patient characteristics, blood pressure level, co-morbidities and frailty, estimated from the electronic frailty index. |

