| Data/ Statistical Analysis **Prognostic modelling**  ***Aim 1 – prognostic model derivation (primary analysis)***  Where feasible and appropriate, flexible parametric survival models will be derived in the CPRD GOLD for each outcome separately. Baseline survival over time will be estimated using the Royston-Parmar approach of restricted cubic splines on the cumulative log hazard scale. In contrast to Cox regression, this allows a smoothed estimate of the baseline survival function to be derived, and the time period of prediction to be varied, facilitating individualised risk prediction. For the primary analysis, a 10-year period of prediction will be considered. Further sensitivity analyses will be conducted examining a 5-year period. Where insufficient data are available, or modelling procedures become prohibitively complex (computationally), simpler approaches such as Cox regression will be considered.  Each drug class (prescribed in the 12 months prior to the index date) will be entered into the model as a binary variable to allow for multiple treatments to be considered in each model. Where appropriate, models will be constructed with all other variables entered as continuous (not categorised) variables, and potential non-linear trends will be examined. Transformations or fractional polynomials will be used if non-linear trends are detected. Where hazard ratios are not proportional, interactions of effects with time will be included. Further interaction terms, identified in an accompanying systematic review, accounting for treatment effects which differ across specific populations may be included. Where appropriate, models will be reduced and candidate predictors selected for inclusion based on p values of association. Time since cohort entry will be used as the underlying time function in each survival model.  In a further analysis, we will extend the modelling process as described above to account for competing risk of death from other causes. This will produce a model that predicts the risk of adverse events from cardiovascular treatment over time, in the real world where individuals might die from other causes and thus prevent cardiovascular treatment adverse events from occurring. We will again use a flexible parametric modelling framework to estimate the sub-distribution hazard and cause-specific cumulative incidence functions.^45^  Missing data will be handled, under a missing at random assumption, using multiple imputation (see below) followed by Rubin’s rules to combine parameter estimates across studies.  Where feasible and appropriate, each model will be internally validated using the bootstrap method, to allow optimism-adjusted estimates of calibration and discrimination performance to be obtained. Adjustment for overfitting will be undertaken using a uniform shrinkage factor identified from bootstrapping, followed by re-estimation of the cumulative baseline sub-distribution hazard function (and thus baseline cumulative incidence function) to maintain overall calibration between observed and predicted risks. Given the large sample size, overfitting is likely to be small (see sample size calculation above). If bootstrapping is computationally infeasible due to the large sample size, then a smaller random sample of the population will be used or alternative internal validation methods employed such as cross validation.  ***Aim 2 – prognostic model validation***  External model validation will be undertaken using data from CPRD Aurum. The accuracy of risk predictions from each model will be assessed with calibration plots and 5 and 10 years, calibration measures (slope, E/O statistics), measures of overall fit (using pseudo-R^2^ estimates) and discrimination measures (C-statistics and D-statistics).  ***Aim 3 – causal inference analysis***  For most of the outcomes described in this proposal, the association and magnitude of effect with treatment is not well defined in randomised controlled trials. We will therefore undertake causal inference work to examine whether modification of treatment could have an important impact on the risk of adverse events using two causal inference methods: propensity score matching and instrumental variable analysis.  For the propensity score analysis, eligible patients will be matched 1:1 at the index date using propensity scores, which indicate the likelihood a patient will be prescribed treatment on the basis of their known (pre-treatment) characteristics and other known information which might influence the decision to treat. Predictors of preventative drug prescription will be explored in a logistic regression model. Matched patients will be compared using the Cox proportional hazards models, but hazard ratios will only be adjusted by factors unbalanced at baseline which are not already included in the propensity score model. Time since cohort entry will be used as the underlying time function in each model.  For the instrumental variable analysis, GP’s previous antihypertensive prescribing preferences will be used as an instrument to predict the likelihood of actual treatment. Risk of adverse events will be estimated in patients attending a GP considered a high prescriber of preventative medication and compared to those attending a GP considered a low prescriber. If the results from the propensity score matching suffer from unmeasured confounding, they will differ from those of the instrumental analysis. If this is the case, these models will be refined with additional factors to achieve better adjustment and matching. Where all approaches provide similar results, we can be more confident that the findings are accurate and reliable.^46^  A similar approach will be applied to secondary outcomes, for example, memory loss which has been hypothesised as being linked with statins^47^ and is a concern of many patients in practice, but there is no evidence to support this association from trials.^48^ We recognise that the evidence base may change for some outcomes over the next few years, and so the need to test the associations between treatment and certain outcomes may change.  *Subgroup and sensitivity analyses*  Where possible and appropriate, analyses of treatment associations will be examined in subgroups of the population. These will include age, sex, baseline blood pressure and cardiovascular risk, by drug type/dose/intensity and past medical history. Subgroup definitions will be agreed by expert opinion or taken from an accompanying systematic review of previous trials, examining the same topic.  Sensitivity analyses will be undertaken examining risk models for outcomes defined according to both hospital and primary care records. We will also explore the impact of our definition of myopathy and muscle pain, focussing on formal diagnostic codes for myopathy only. Models utilising a 5-year follow-up will be examined as a further sensitivity analysis. The primary analyses will examine the association between treatment and outcomes, assuming treatments are not altered or modified in the future. Where possible, sensitivity analyses will examine treatment entered as time varying covariates, and censor patients who have treatments removed or switched following the index date. |

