| Plans for addressing missing data There is potential for missing data in this study, particularly with variables such as ethnicity which are recorded with varying degrees of accuracy in routine practice. Because this analysis is focused on treatment for prevention of cardiovascular disease, accurate selection of the sample population is important and therefore any patients with insufficient data available to define their blood pressure or cardiovascular risk status at baseline (index date) will be excluded. Where there is no record of blood pressure lowering, statin or antiplatelet treatment, it will be assumed the patients were not exposed to blood pressure lowering, statin or antiplatelet treatment.  Patient eligibility includes only using ‘acceptable patients’ in the analysis, and therefore there is no need to impute age and sex. Where there is no record of smoking history or alcohol consumption, patients will be assumed to be non-smokers and non-drinkers. Likewise, those with no record of co-morbidities will be assumed to have no history of these conditions. All other covariates (including BMI, ethnicity and IMD) used in the prognostic or casual inference modelling will be imputed using multiple imputation. BMI and will be treated as a continuous variable.  All analyses of treatment associations with outcomes will be conducted by intention-to-treat, and patients moving practice after the index date (and therefore being lost to follow-up) will be censored at the point at which they are no longer active in the database. |

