| List of Appendices Appendix 1. Code lists for the primary outcomes |
| Amendments **Amendment 1 – 19/05/2019 (approved)**  **We clarify that aims 1 and 2 (prognostic model derivation and validation) of the study should include the whole population independently of whether patients are new or old users of preventative treatment; the causal inference analyses will focus on new users only:**  *L. Definition of the study population*  Patients will be excluded if they meet the following criteria:  Previous prescription of the exposure variable (antihypertensive, statin or antiplatelet; for causal inference analyses only)  **Amendment 2 – 28/06/2021 (approved 05/07/2021)**  **We have made the following revisions aimed at simplifying the analysis plan in light of the very large sample size and computational time required to conduct each analysis:** *C. Technical Summary / E. Objectives, Specific Aims and Rationale* Aims:  3) Use causal inference methods (multivariable regression, propensity score adjustment/matching, instrumental variable analysis) to examine whether modification of treatment could have an important impact on the risk of adverse events.  *L. Definition of the study population*  Study entry criteria – Patients will enter the cohort on the index date, defined as:   \| **Exposure** \| Antihypertensive therapy \| Statin therapy \| Antiplatelet therapy \| \| --- \| --- \| --- \| --- \| \| **Index date definition** \| 12 months after the first systolic blood pressure reading ≥130 mm Hg \| 12 months after the first coded or calculated CVD risk of ≥5% (equivalent to age ≥50 years for men and ≥60 years for women) \| 3 months after first CVD event \|   *N. Exposures, Outcomes and Covariates*  Positive controls are outcomes know to be affected by treatment (e.g. cardiovascular disease, death)  For causal inference analyses (only), sensitivity analyses will explore outcomes defined more broadly using primary care codes as well. *O. Data/ Statistical Analysis* We no longer plan to conduct an internal validation of the prediction models. The following text from the protocol is therefore redundant:  Where feasible and appropriate, each model will be internally validated using the bootstrap method, to allow optimism-adjusted estimates of calibration and discrimination performance to be obtained. Adjustment for overfitting will be undertaken using a uniform shrinkage factor identified from bootstrapping, followed by re-estimation of the cumulative baseline sub-distribution hazard function (and thus baseline cumulative incidence function) to maintain overall calibration between observed and predicted risks. Given the large sample size, overfitting is likely to be small (see sample size calculation above). If bootstrapping is computationally infeasible due to the large sample size, then a smaller random sample of the population will be used or alternative internal validation methods employed such as cross validation.  *Aim 3 – causal inference analysis*  For most of the outcomes described in this proposal, the association and magnitude of effect with treatment is not well defined in randomised controlled trials. We will therefore undertake causal inference work to examine whether modification of treatment could have an important impact on the risk of adverse events using two causal inference methods: multivariable adjustment, propensity score adjustment/matching and instrumental variable analysis.  For the analysis using multivariable adjustment, Cox proportional hazards models will be used to compare adverse event rates in each experimental group. Estimates will be adjusted for pre-specified variables thought to confound the relationship between treatment and adverse events.  For the analysis using propensity scores, we will conduct separate analyses adjusting for propensity score and matching via propensity score.  *Subgroup and sensitivity analyses*  Where possible and appropriate, analyses of treatment associations will be examined in subgroups of the population. These will include age, sex, baseline blood pressure and cardiovascular risk, by drug type/dose/intensity and past medical history. Subgroup definitions will be agreed by expert opinion or taken from an accompanying systematic review of previous trials, examining the same topic. For computational reasons (whereby only one imputation model is required for all subgroup analyses of each outcome), these analyses will only be undertaken using propensity score adjustment. *P. Plan for addressing confounding* Two approaches will be taken to determine whether observed associations are potentially subject to residual confounding.^46^ Where all approaches provide similar results, we can be more confident that the findings are accurate and reliable. Further steps will be taken to examine the validity of treatment effect estimates using positive and negative controls: the impact of treatment on an outcome known to be affected by treatment (e.g. cardiovascular disease and death; positive controls)  **Amendment 3 – 25.11.2021**  **We have added exploratory analyses using supervised machine learning approaches to address missing data and deal with confounding by indication in the causal inference analyses.** O. Data/ Statistical Analysis ***Aim 3 – causal inference analysis***  For most of the outcomes described in this proposal, the association and magnitude of effect with treatment is not well defined in randomised controlled trials. We will therefore undertake causal inference work to examine whether modification of treatment could have an important impact on the risk of adverse events using two causal inference methods: propensity score matching and instrumental variable analysis.  For the propensity score analysis, eligible patients will be matched 1:1 at the index date using propensity scores, which indicate the likelihood a patient will be prescribed treatment on the basis of their known (pre-treatment) characteristics and other known information which might influence the decision to treat. Predictors of preventative drug prescription will be explored in a logistic regression model. Matched patients will be compared using the Cox proportional hazards models, but hazard ratios will only be adjusted by factors unbalanced at baseline which are not already included in the propensity score model. Time since cohort entry will be used as the underlying time function in each model.  For the instrumental variable analysis, GP’s previous antihypertensive prescribing preferences will be used as an instrument to predict the likelihood of actual treatment. Risk of adverse events will be estimated in patients attending a GP considered a high prescriber of preventative medication and compared to those attending a GP considered a low prescriber. If the results from the propensity score matching suffer from unmeasured confounding, they will differ from those of the instrumental analysis. If this is the case, these models will be refined with additional factors to achieve better adjustment and matching. Where all approaches provide similar results, we can be more confident that the findings are accurate and reliable.^46^  Generative Adversarial Networks (GAN) will also be used to impute missing counterfactual data (unobserved effects of untaken treatments) on an individual level. GAN models are a class of machine learning frameworks that involves the simultaneous training of a pair of deep neural networks in competition with each other. The idea is that the first network, the generator, generates synthetic data samples that are similar to the original samples, while the second network, the discriminator, evaluates the authenticity of the generated samples [1]. Data similarity and fidelity are usually evaluated using well-known metrics such as Maximum Mean Discrepancies [2] and Jensen-Shannon Divergence [3]. While GAN’s initial uses were for imaging applications, its generative capabilities make it naturally suitable for generating missing values that can be used to impute the original samples.  In this work, we build on the intuition that treatment effects estimation and causal inference are a missing data problem, where counterfactuals (unobserved effects of untaken treatments) are missing [4]. Specifically, we plan to use GAN to impute missing counterfactual data, for the samples available in CPRD. By modifying the generator’s goal to accurately impute missing data, and the discriminator’s goal to distinguish between observed and imputed counterfactual values for the same patient record. The model can generate the missing data conditional on the observed values and assigned treatment for each patient as seen in [5, 6]. While useful, the work of [5, 6] are not compatible for time-series data nor for estimating multiple treatment effects, which limits its use in real-life treatment applications. Therefore, we plan to extend such previous works to make them compatible for multiple treatment options and for time-series data to allow for long-term treatment (antihypertensives, statins, antiplatelets) estimation effects for multi-morbid populations as initially proposed in this project.  The proposed GAN approach does not generate new patient samples, but rather generates counterfactual (missing component) conditioned on observed factual data, and outputs a complete record with both factual and counterfactual outcomes to allow for treatment effect estimation for each patient. This approach is naturally immune to re-identification attacks since no new samples are generated, but we will run privacy checks and measures within the data to verify that the model is not copying potential outcomes from patients in the training sample. Example privacy measures that we plan to apply include empirical evaluations such as mathematical privacy definitions such as identifiability [7] that quantifies the probability of re-identification to ensure that no combination of attributes could reveal the identity of a patient. Other privacy evaluation methods include testing that the model is robust against membership inference attacks, where an attacker attempts to determine if a specific patient was used in the training set of the model [8]. Lastly, we will experiment with strict theoretical guarantees such as differential privacy which allow for the model to learn almost nothing about an individual while learning useful information about a population [9].  **References**  [1] Ian Goodfellow, Jean Pouget-Abadie, Mehdi Mirza, Bing Xu, David Warde-Farley, Sherjil Ozair, Aaron Courville, and Yoshua Bengio. Generative adversarial nets. *Advances in neural information processing systems*, 27:2672–2680, 2014.  [2] Arthur Gretton, Karsten M Borgwardt, Malte J Rasch, Bernhard Sch¨olkopf, and Alexander Smola. A kernel two-sample test. *The Journal of Machine Learning Research*, 13(1):723–773, 2012.  [3] AP Majtey, PW Lamberti, and DP Prato. Jensen-shannon divergence as a measure of distinguishability between mixed quantum states. *Physical Review A*, 72(5):052310, 2005.  [4] Peng Ding and Fan Li. Causal inference: A missing data perspective. *Statistical Science*, 33(2):214– 237, 2018.  [5] Jinsung Yoon, James Jordon, and Mihaela Schaar. Gain: Missing data imputation using generative adversarial nets. In *International Conference on Machine Learning*, pages 5689–5698. PMLR, 2018.  [6] Jinsung Yoon, James Jordon, and Mihaela van der Schaar. Ganite: Estimation of individualized treatment effects using generative adversarial nets. In *International Conference on Learning Representations*, 2018.  [7] Jinsung Yoon, Lydia N Drumright, and Mihaela Van Der Schaar. Anonymization through data synthesis using generative adversarial networks (ads-gan). *IEEE journal of biomedical and health informatics*, 24(8):2378–2388, 2020.  [8] Reza Shokri, Marco Stronati, Congzheng Song, and Vitaly Shmatikov. Membership inference attacks against machine learning models. In *2017 IEEE Symposium on Security and Privacy (SP)*, pages 3–18. IEEE, 2017.  [9] Cynthia Dwork, Aaron Roth, et al. The algorithmic foundations of differential privacy. *Found. Trends Theor. Comput. Sci.*, 9(3-4):211–407, 2014.  **Amendment 4 – 30.11.2022**  **Added University of Birmingham to the list of data processors.** |

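### Antiplatelet causal analyses: users of bought aspirin can be classed as unexposed or as new users, and no planned check targets the resulting bias

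*Protocol*

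**What the plan says.** One rule covers all three drug classes. Under *Plans for addressing missing data* the Protocol states that, in the absence of any record of such treatment, "it will be assumed the patients were not exposed to blood pressure lowering, statin or antiplatelet treatment".

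The antiplatelet exposure list under *Exposures, Outcomes and Covariates* reads "Aspirin Clopidogrel Dipyridamole Ticagrelor Prasugrel". The antiplatelet cohort is entered "3 months after first CVD event" (*Definition of the Study population*).

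Elsewhere exposure and prior use are tied to prescriptions. Under *Data/Statistical Analysis*, for the prognostic models: "Each drug class (prescribed in the 12 months prior to the index date) will be entered into the model as a binary variable". The exclusion that defines new users is "Previous prescription of the exposure variable (antihypertensive, statin or antiplatelet; for causal inference analyses only" (Amendment 1). The propensity score is described as the likelihood of being prescribed treatment.

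The sample size for the causal analyses assumes "an event rate of at least 0.5% per year in the non-exposed group", a 10% higher rate with treatment, 90% power and an alpha of 0.05. It arrives at 4,634 events in 88,380 patients.

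**The concern.** For drugs obtained only on prescription, the prescribing record is a reasonable measure of exposure. Aspirin differs because it can also be bought, and patients who have just had a first CVD event have a reason to take it. Two misclassifications follow. A patient taking bought aspirin with no record becomes a control. A patient who bought aspirin before a first prescription passes the previous-prescription exclusion and is analysed as a new user.

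The first matters most. If some controls are really exposed, the contrast shrinks and the harm is understated. That is the unfavourable direction for a study whose results are meant to feed a public harm calculator, and intracerebral haemorrhage is one of its primary outcomes. Matching and covariate adjustment work on who was prescribed treatment and cannot repair a wrong exposure label.

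**Working it through.** **Inputs from the Protocol (*Sample size considerations*, *Feasibility counts*).** Hazard ratio (HR) 1.10; alpha 0.05; power 90%; equal groups; control rate at least 0.5% per year; 4,634 events; 88,380 patients; about 1,200 intracranial haemorrhages expected among 3.3 million eligible patients in CPRD GOLD.

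**Assumed inputs.** The share q of controls taking bought aspirin is not in the Protocol; 5%, 10% and 20% are used. Alpha is taken as two-sided and follow-up as 10 years, because these reproduce the stated figures.

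**Step 1: reproduce the plan's figure.** Freedman's formula gives events = (1.960 + 1.282)² × [(1.10 + 1)/(1.10 − 1)]² = 10.507 × 441 = 4,634, an exact match. Over 10 years the control risk is 5% and the treated risk is 1 − 0.95^1.1 = 5.486%, with a mean of 5.243%. Then 4,634 / 0.05243 ≈ 88,384 patients, against 88,380 stated. The calculation makes no allowance for exposed patients among the controls.

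**Step 2: dilution from contaminated controls.** If a share q of controls is truly exposed and otherwise like the rest, the control rate rises by the factor 1 + q(HR − 1), so

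observed HR = HR / [1 + q(HR − 1)].

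At HR 1.10 this is 1.10 / (1 + 0.10q).

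| q (assumed) | Observed HR, true 1.10 | Observed HR, true 1.50 (illustration) | Power at 4,634 events, true 1.10 |
|---|---|---|---|
| 0% | 1.100 | 1.50 | 90.0% |
| 5% | 1.095 | 1.46 | 86.7% |
| 10% | 1.089 | 1.43 | 82.8% |
| 20% | 1.078 | 1.36 | 72.9% |

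Power = Φ[ln(observed HR) × √events / 2 − 1.96]. At q = 10% and a true HR of 1.10, ln(1.0891)/ln(1.10) = 0.896, so about 10% of the log hazard ratio is lost. More patients can restore power but leave the estimate biased.

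**Step 3: which outcomes the power column describes.** It applies only to an outcome that reaches 4,634 events. The only intracranial haemorrhage count given is about 1,200, in the whole eligible GOLD population. Even if all 1,200 fell in one evenly split comparison, power at HR 1.10 would be Φ(0.0953 × 17.32 − 1.96) = 37.9%, and 31.5% at q = 10%. No event count is given for gastrointestinal haemorrhage.

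**Step 4: would a planned check catch it?**
- The sensitivity analyses cover primary-care outcome codes, the myopathy definition, 5-year follow-up, and time-varying treatment with censoring on removal or switching. None concerns unrecorded exposure.
- The instrument is prescribing preference, so buyers among low prescribers' patients dilute that contrast too. Agreement between the two methods would not exclude the problem.
- Negative controls look for spurious effects, not for a lost effect.
- Positive controls (CVD, and death under Amendment 2) would be attenuated by heavy contamination, but the stated criterion is only that an association is present. Modest dilution would pass.
- The limitations section covers under-recorded outcomes and unmeasured confounding, but not misclassified exposure.

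**The case against.** The strongest reply is that the decisive facts lie outside the Protocol. It does not say that aspirin is bought, how often this happens after a first CVD event, or how well primary care records it. That stands. A reader might infer that the control group has been shown to contain aspirin users and that the bleeding effect is diluted. The Protocol supports only that its rules allow this.

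Second, the missing-data rule speaks of no record of treatment, not of no prescription. A coded entry of bought aspirin could count as a record. This also stands for that sentence, but the new-user exclusion and the exposure definition in the models refer to prescriptions, so the wording needs settling either way. Exposure code lists may properly sit elsewhere; the point here is the stated rule, not an absent list.

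Third, a reader might take the fall from 90% to 83% power as the loss for the primary bleeding outcome. The Protocol's own count of about 1,200 intracranial haemorrhages rules that out.

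Fourth, a reader might suppose that both misclassifications act towards the null. Only the contaminated-control error has been worked through, and its direction needs buyers to resemble non-users in bleeding risk. The direction of the prior-buyer error has not been shown.

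Finally, the shifts are modest: 1.10 becomes 1.089 at q = 10%. That limits the weight of the point but does not answer it, since the plan treats a 10% increase as clinically significant.

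**Conclusion.** The point holds in a limited form. For the antiplatelet causal analyses, the no-record rule and the prescription-only new-user exclusion can put users of non-prescribed aspirin among controls or new users, and no planned check is aimed at this. Contaminated controls bias the bleeding hazard ratios towards the null if buyers otherwise resemble non-users; if they differ, confounding is added and the direction is not assured.

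The amount cannot be determined from the Protocol and could be small. The figures above are conditional on an assumed q. The conclusion also rests on the general knowledge that aspirin is sold without prescription. It is confined to aspirin and does not extend to the antihypertensive or statin analyses.

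**What to change.** For the antiplatelet cohort, replace the blanket no-record rule with the following:

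1. Any primary-care code for non-prescribed aspirin counts as a record of treatment.
2. Patients with such a code before the qualifying CVD event are excluded from the new-user cohort.
3. Patients with such a code in the exposure window are removed from the unexposed group: excluded in the main analysis and classified as exposed in a sensitivity analysis.
4. The bleeding hazard ratios are reported with a bias table at assumed unrecorded use of 5%, 10% and 20% in controls. Inverting the formula above, corrected HR = observed HR × (1 − q) / (1 − q × observed HR).
5. The remaining misclassification is named as a limitation.

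The cost is one additional code list, applied to primary-care data already requested, and a short table. A few patients are dropped. Because recording of bought aspirin is incomplete, the bias is reduced and not removed, which is why the bias table is needed alongside the codes.
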